## 3.4. Sample Size Determinations

The sample size was estimated by G power version 3.1.9.7. Assumptions used to calculate the required sample size were: precision of 5%, power of 80%, an effect size of 0.25, and we expect a mean birth weight change of 100 gm (the primary outcome) in the intervention groups (from 2975 g to 3075 g) based on previous studies. Design effects of 2 and 15% non-response rates were also considered. The total sample size was 348 pregnant women (116 per each of the three study arms).

The sample size for each study cluster (kebele) will be allocated based on the proportion of their respective population. Accordingly, a total of eighteen clusters (kebeles) will be selected. From Mana and Seka districts eight and ten clusters (kebeles) respectively.

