## 3.8. Data collection and instruments

The data will be collected in two phases. After the home-to-the-home census of eligible pregnant mothers enrolment, the baseline data will be collected by using pre-tested structured questioners, and guidance equations. Accordingly, data on socio-demographic characteristics, obstetrics history, MUAC, Hgb level, and 24-hour recall minimum women dietary diversity scores (FAO and FHI guideline 2016) will be collected. To get the best possible information, first, the mother will be asked to narrate what she remembers followed by probes to ascertain that no meal or snack will be left out. After all, a detailed list of all the ingredients of the dishes, snacks, or other foods consumed will be generated and grouped into ten. The end-line data will be collected after the mother gave birth, just within 24 hrs.

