## 3.13. Hemoglobin level Determination

Hemoglobin will be measured at baseline and end line using a portable, battery-operated photometer (HemoCue). After swiping the site with disinfectant, a finger prick will be made to obtain blood for hemoglobin measurement. The first two drops will be swapped away and the third drop will be used to fill the micro cuvette for reading the hemoglobin. The machine will be calibrated daily with a reference microcuvette provided with the machine. A trained and skilled laboratory technologist will be responsible for the collection of blood samples and hemoglobin determination.

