## 3.14. Statistical analysis

Data will be entered into Epi-data Version 3.1 for cleaning and sorting and then exported to SPSS version 20 for analysis. First, we will present descriptive information on the socio-demography of enrolled mothers, and then, baseline measurements will be compared between allocation groups by using mean difference or chi-squares. Comparison of the KAP scores, birth weight, hemoglobin level, and GWG, differences among the study arms will be done using ANOVA. The normality assumptions and the homogeneity of variance will be checked using a Q-Q plot and Levene’s test. The linear GEE regression analyses will be used to test the effects of the interventions on feto-maternal outcomes (birth weight and hemoglobin level) of difference in difference.

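### Hemoglobin is read at baseline and end line, but neither planned test adjusts for the baseline reading, so both are less precise than they need be and can disagree

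*Protocol*

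**What the plan says.** Protocol section 3.13 states: "Hemoglobin will be measured at baseline and end line using a portable, battery-operated photometer (HemoCue"). Section 3.8 confirms the first reading, listing among the baseline items "data on socio-demographic characteristics, obstetrics history, MUAC, Hgb level, and 24-hour recall minimum women dietary diversity scores". It places end-line collection within 24 hours of birth. Each woman therefore has a first-trimester and a delivery value.

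Section 3.14 gives hemoglobin two analyses:

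- An ANOVA: "Comparison of the KAP scores, birth weight, hemoglobin level, and GWG, differences among the study arms will be done using ANOVA".
- A linear GEE: "The linear GEE regression analyses will be used to test the effects of the interventions on feto-maternal outcomes (birth weight and hemoglobin level) of difference" (the phrase completes as difference in difference).

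Neither sentence names baseline hemoglobin as a covariate, and section 3.6.2 does not list it among the independent variables. Section 3.14 uses baseline data in one other way: "baseline measurements will be compared between allocation groups by using mean difference or chi-squares". That compares the arms at the start and does not adjust the result.

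**The concern.** An ANOVA of end-line level ignores the baseline value. A difference in difference subtracts it in full, as if the slope of end-line on baseline hemoglobin were exactly 1. A model that estimates the slope does at least as well as either, and better whenever r lies strictly between 0 and 1.

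Hemoglobin is one of only two outcomes that section 3.14 assigns to the effect model. Anemia is a listed dependent variable (section 3.6.1) and bears on the nutritional-status objective (section 2.2). With six kebeles per arm, some chance difference in mean baseline hemoglobin is to be expected. The two planned analyses respond to it in opposite directions, and section 3.14 does not say which one governs.

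**Working it through.** **Inputs from the protocol.** Two hemoglobin readings per woman (3.13); 116 women per arm, 18 kebeles, design effect 2 and 15% non-response (3.4); six kebeles per arm (3.5).

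**Not in the protocol.** It gives no correlation, SD, ICC, effect size or power for hemoglobin, so there is no stated hemoglobin figure to reproduce. The sample size of 348 rests on birth weight ("we expect a mean birth weight change of 100 gm (the primary outcome) in the intervention groups (from 2975 g to 3075 g") and is not used below beyond the number per arm.

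**Assumptions.** Correlation r between the two readings, shown over a range; equal variance at both times; a 0.5 SD arm difference for the power illustration; and the design effect and non-response rate borrowed from the birth-weight calculation.

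**Step 1: variance of a pairwise arm difference**, in units of 2σ²/n:

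- end-line level: 1
- difference in difference: 2(1−r)
- baseline-adjusted: 1−r²

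The saving from adjustment is 1 − (1−r²)/[2(1−r)] = (1−r)/2 against difference in difference, and 1 − (1−r²) = r² against level.

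| r | Level | Difference in difference | Adjusted | Saving v difference in difference | Saving v level |
|---|---|---|---|---|---|
| 0.3 | 1 | 1.40 | 0.91 | 35% | 9% |
| 0.5 | 1 | 1.00 | 0.75 | 25% | 25% |
| 0.7 | 1 | 0.60 | 0.51 | 15% | 49% |

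Below r = 0.5, difference in difference is less precise than ignoring the baseline altogether.

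**Step 2: check under clustering.** A two-arm simulation used six kebeles per arm, 16 women each, ICC 0.055, the same r at kebele and woman level, no true effect and 4,000 runs. The ICC follows from design effect 2 with 116/6 = 19.3 women per kebele: 1/(19.3−1) = 0.055. The variance ratio of difference in difference to adjusted was 1.51, 1.32 and 1.17 at r = 0.3, 0.5 and 0.7. The formula 2/(1+r) gives 1.54, 1.33 and 1.18. All three estimators averaged within 0.006 SD of zero, so none is biased on average.

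**Step 3: power for one fixed effect.** Effective n per arm = 116 × 0.85 / 2 = 49.3. The standard error of a level difference is √(2/49.3) = 0.201 SD. Two-sided 5% power for a 0.5 SD difference is Φ(0.5/(0.201√v) − 1.96), with v from step 1 (0.40 for difference in difference and 0.36 for adjusted at r = 0.8).

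| r | Level | Difference in difference | Adjusted | Gain v difference in difference |
|---|---|---|---|---|
| 0.3 | 69.9% | 55.5% | 74.0% | 18.5 points |
| 0.5 | 69.9% | 69.9% | 81.8% | 11.9 points |
| 0.7 | 69.9% | 89.3% | 93.5% | 4.2 points |
| 0.8 | 69.9% | 97.5% | 98.5% | 1.0 point |

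**Step 4: chance imbalance.** Given a realised baseline difference D between arms, the level comparison shifts by +rD and the difference in difference by −(1−r)D. The adjusted estimate shifts by about 0. At r = 0.5 the simulated slopes on D were 0.50, −0.50 and 0.00. The two planned estimates therefore differ by rD + (1−r)D = D. The standard error of D is also about 0.20 SD. A typical imbalance moves the difference in difference by 0.7 × 0.20 = 0.14 SD at r = 0.3 and by 0.3 × 0.20 = 0.06 SD at r = 0.7.

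**The case against.** **A reader might infer that the baseline reading is wasted, or that the planned results would be biased.** The documents support neither. A difference in difference uses each baseline value, though not efficiently. Both planned estimators are unbiased on average under randomisation, and the shifts in step 4 are conditional on the imbalance that happens to occur.

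**Covariates are usually left to the SAP.** This is fair for a covariate list. Here, however, the protocol fixes the contrast itself as difference in difference, and an SAP that follows it inherits the less efficient estimator. A repeated-measures model with baseline arm means constrained equal would come close to the adjusted model, but section 3.14 does not state that constraint.

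**The ANOVA sentence is ambiguous.** It could refer to end-line levels or to changes. If it means changes, it shares the loss of the difference in difference instead of that of the level comparison.

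**The power gain is easy to overstate.** It is tempting to set each planned test at the protocol's 80% and count the gain from there. That 80% belongs to birth weight, and for one fixed hemoglobin effect both tests can have 80% power only at r = 0.5. With the level test alone set at 80%, difference in difference against adjusted is 92.5% v 96.2% at r = 0.66 and 97.7% v 98.9% at r = 0.75. The gain over difference in difference is therefore small once r exceeds about 0.7. No document supplies r.

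**Missing baselines.** A repeated-measures GEE can use a woman who has only an end-line reading, whereas the adjusted model drops her unless her baseline is imputed. This stands and is counted as a cost.

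**Limits of the check.** The simulation compared the variances of point estimates. It did not test GEE standard errors with 18 clusters.

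**Conclusion.** The point holds as one of efficiency and robustness for a non-primary outcome. Section 3.14 commits hemoglobin to two analyses that do not adjust for a baseline value already collected. For any r strictly between 0 and 1, and equal variances, both are less precise than the adjusted model. Over the assumed range r = 0.3 to 0.7, the variance saving is 35% down to 15% against difference in difference, and 9% up to 49% against the level comparison. The two planned estimates also differ by the whole of any chance baseline difference between arms, so they can lead to different conclusions from the same data. The size of the power gain depends on r and on the effect assumed. The validity of the trial and the birth-weight analysis are not in question here.

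**What to change.** In section 3.14, make the hemoglobin effect analysis one linear GEE clustered on kebele, with end-line hemoglobin as the outcome and study arm and each woman's baseline hemoglobin as covariates. Report the adjusted arm differences as the hemoglobin result, and give change from baseline as description only. Drop hemoglobin from the ANOVA sentence, or mark that comparison as descriptive.

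State how a missing baseline reading is handled: either a simple imputation of the covariate, or exclusion of the woman with the number reported.

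The same form may be used for MUAC and dietary diversity score if they are analysed as continuous outcomes. This is only a suggestion, since section 3.14 names no effect model for them, and a linear model would not suit them once they are cut into yes/no indicators.

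The cost is a short edit to section 3.14, one degree of freedom and the missing-baseline rule. No new data, visits or women are needed.

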## 3.5. Sampling procedures

Two districts (woreda) that could represent the two known agroecological areas of the Jimma zone will be selected. Accordingly, Mana from predominantly coffee-growing districts and Seka Chekorsa from grain and crop-growing districts were selected purposively for management and logistical reasons. Then, non-adjacent clusters or kebeles (the smallest administrative units) will be selected from both districts to have buffer zones**.** Accordingly, a total of 18 clusters (8 from Mana and 10 from Seka chekorsa) districts will be selected. Using the randomized complete block design; the clusters (kebeles) will be grouped into two blocks based on their agroecological areas (mainly coffee or grain producing). Finally, from both blocks clusters will be randomly assigned to the three study arms (husband, Peers, and control). Thus, Nase, Bidaru toli, Dimtu (of Seka), Doyo toil, Gudata bula, and Lemi Lelisa clusters(kebeles) will be assigned to the husband group. While, Siba bake, Buyo kechema, Meti, Bore, Bebela kosa, and Haro clusters will be assigned to the peer group. Likewise, Komo hare, Gepa seden, Wakito madalu, Kamise waraba, kore Lelisa, and kenteri clusters will be assigned to the control group.

Regarding the sample size allocation, it was proportionally to the population size of respective districts and kebeles (clusters). A total of 348 first-trimester pregnant women will be enrolled at baseline, 144 women will be from the mana district (48 women in each arm), and 204 women will be from the Seka-chekorsa district (68 women in each arm). This means that a total of 116 1^st^ trimester pregnant women per the three study arms will be enrolled. All of the first-trimester pregnant women who will fulfill the inclusion criteria in each cluster will be enrolled until the desired or allocated number will be achieved.

[figure not shown]

Figure 2. Map of the study area with selected study clusters (kebeles) of both districts (Seka and Mana) source: Generated using ArcGIS software version 10.3 from ETHIO-GIS, 2014 database.

Jimma zone

21 Districts ( woredas)

Goma,

Limu kosa

Mana

Gera

Gumay

Limu seka

Boter –tolay

Chora- boter

Shebe- sombo

Non benja

Omo- Nada, Omo-Beyam

Sekachekorsa

Mancho

Dedo

Kersa

Tiroafata

Sokoru,

Santama

Sigimo

Gatira

Predominantly Grain/crops producing districts.

11 districts

---

Predominantly coffee growing districts,

10 districts

Mana district selected

Mana district

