26 kebeles (clusters) total

Sekachekorsa district

37 kebeles (clusters) total

10 Clusters selected

8 Clusters selected

Coupled Intervention arm

3 clusters

Coupled intervention arm 3clusters

Mothers with their peers arm

4 clusters

Control arm

3clusters

Mothers with their peers arm

2 clusters

Control arm

3 clusters

Figure 3. Shows that the sampling procedure for the effect of home gardening and social behavioral change communication on feto-maternal outcomes in Jimma zone, South West Ethiopia, 2019.

Total=18 clusters

1. Husband intervention arm=6 clusters/kebeles (Nese, Gepa seden, Dimtu, Doyo toil, Gudata bula, Lemi lelise
2. Mothers with their peer intervention arm=6 clusters/kebeles (Siba beke, Meti,Buyo kechema, Bore,Babala kosa, Haro
3. Control arm = 6 clusters/kebeles (Bidaru tuli,Komo hare,Wakito medalu,Kemise waraba,Kore lelisa,Kenteri

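### The linear GEE rests on 18 kebeles (6 per arm) with no clustering unit or small-sample method named; an uncorrected kebele-clustered test at nominal 5% would have about 10–15% error

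*Protocol*

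**What the plan says.** - **Units randomised.** Section 3.4: "Accordingly, a total of eighteen clusters (kebeles) will be selected". Section 3.5: "from both blocks clusters will be randomly assigned to the three study arms (husband, Peers, and control"). The list under Figure 3 gives six kebeles to each arm, for example "Control arm = 6 clusters/kebeles".
- **Error rate.** The sizing in section 3.4 uses "precision of 5%, power of 80%, an effect size of 0.25", a design effect of 2 and 15% non-response, and arrives at 348 women, 116 per arm. The word used is precision. I read it as a two-sided 5% significance level, which the protocol does not spell out.
- **Test.** Section 3.14: "The linear GEE regression analyses will be used to test the effects of the interventions on feto-maternal outcomes". The outcomes named are birth weight and hemoglobin, in difference-in-difference form, with the data "exported to SPSS version 20 for analysis". The same section also compares birth weight and hemoglobin across arms by ANOVA, with no cluster term.
- **Not stated.** Section 3.14 does not give the GEE's clustering unit, working correlation, variance estimator, reference distribution or any small-sample correction. Section 3.2.2 makes the individual mother the unit of analysis.

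**The concern.** GEE inference normally uses a robust (sandwich) variance and a normal or chi-square reference. Both are justified when there are many independent clusters, and here there are 6 per arm. With so few, the sandwich variance is biased downward because each arm's mean is estimated from the same six kebeles. The normal reference also ignores that the variance rests on few degrees of freedom. Both faults push towards false positives and narrow intervals.

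This is distinct from the ANOVA ignoring clustering. Naming kebele as the GEE cluster is the obvious first repair, and on its own it would still leave the test well above 5%. At stake is how often an ineffective intervention would be declared effective on the primary outcome.

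**Working it through.** **Plan's own figure.** The protocol gives a nominal 5% but no achieved error rate, so there is none to reproduce. The sample size of 348 enters below only through the cluster size. (It does not follow exactly from the stated inputs: Cohen's f = 0.25 with three arms needs 159, and 159 × 2 × 1.15 = 366 or 159 × 2 / 0.85 = 374. That is a separate matter.)

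**Inputs.** 18 kebeles, 6 per arm; 348 women; design effect 2; 15% loss (sections 3.4 and 3.5). Mean kebele size is 348/18 = 19.3. Implied ICC = (2 − 1)/(19.3 − 1) = 0.055; this is derived, not stated.

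**Step 1: one arm versus control, exact for equal kebele sizes.** With J = 6 kebeles per arm, the uncorrected sandwich estimates the variance of an arm mean as Σ(kebele mean − arm mean)²/36. That is (J − 1)/J = 5/6 of the unbiased estimate. The z test therefore rejects when a t statistic on 10 df exceeds 1.96 × √(5/6) = 1.789, and P(|t₁₀| > 1.789) = 10.4%. The correct cut-off on 10 df is 2.228, so the interval is 1.789/2.228 = 0.80 of its proper width. The ICC does not appear in this calculation.

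**Step 2: null simulations with kebele as the cluster and uncorrected robust variance, nominal 5%.**

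| Setting | One arm vs control | Three-arm Wald test |
|---|---|---|
| Figure 3 kebele counts, section 3.5 quotas, 15% loss, ICC 0.01–0.10 | 10.3–11.1% | 14.8–15.5% |
| Equal or unequal kebele sizes, independence or exchangeable weights, ICC 0.01–0.10 | 9.8–12.1% | 14–18% |
| Fitted individual-level GEE, ICC 0.055, no district term | 9.9–10.6% | 14.3% |
| Same, with district term | 12.1–12.5% | 18.3% |
| Hemoglobin difference-in-difference, kebele as cluster | 10.8% | 15.3% |

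The chance that at least one of the two intervention arms differs from control at nominal 5% is 18–19% in the first setting. That figure also contains ordinary multiplicity and should not be charged to the sandwich variance alone.

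**Step 3: kebele ignored (a single measurement such as birth weight, ICC 0.055).** Simulation gives about 16% for a pairwise comparison of women and about 21% for one-way ANOVA. A large-sample check with design effect 2 and no loss agrees: P(|Z| > 1.96/√2) = 16.6%, and for the 2-df test exp(−5.99/4) = 22.4%.

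**Step 4: which remedies restore 5%.**
- F test on the 18 kebele means (2 and 15 df): 4.9–5.1%.
- Pooled intervention versus control, t on 16 df: 5.1%.
- Hemoglobin change with variance × 6/5 and t on 10 df: 5.3%.
- Mancl–DeRouen-type correction: 5.3–6.3% with z, and 3.3–3.9% with t on 10 df (conservative).
- Only the reference changed, to t on 15 df, with variance uncorrected: 7.5–9.6%. Not enough.

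**Step 5: power of a valid test.** Read 0.25 as Cohen's f with both intervention arms equal, so the standardised difference is 0.25 × 3/√2 = 0.53. After 15% loss there are 348 × 0.85/18 = 16.4 women per kebele. The variance of a kebele mean is 0.0545 + 0.9455/16.4 = 0.112 in SD² units. Noncentrality is 18 × 0.0625/0.112 = 10.0, and the F(2,15) test has 73% power. Simulation with the planned unequal kebele sizes gives 72%, against an inflated 87% for the uncorrected Wald test. For the two intervention arms pooled, the figures are 84% and 90%.

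**The case against.** The strongest objection is that section 3.14 is silent rather than wrong. It names no sandwich estimator, Wald test or normal reference. Such details are commonly settled in a statistical analysis plan, which may exist. GEE can be used with 18 clusters if the variance is corrected. Most of this stands. A reader might infer that the protocol prescribes uncorrected large-sample tests, that it labels the GEE confirmatory, or that its error rate simply is 10–15%. The text supports none of these, and the 5% itself appears only as a precision. Citing SPSS does not show which options would be chosen.

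A second objection is that kebele may not be the intended GEE cluster. The mother is called the unit of analysis, and a difference-in-difference also fits repeated measures within a woman. That is fair, but it does not rescue the plan: for birth weight that reading gives about 16–21% error at ICC 0.055.

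What remains is that the protocol has already chosen an estimator that relies on many clusters, for a design with six per arm. Each plain reading of section 3.14 exceeds 5% unless a correction that the document does not mention is added.

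**Conclusion.** The point holds in conditional form. With kebele as the GEE cluster, uncorrected robust variance and a normal or chi-square reference, nominal 5% becomes about 10–11% for one arm versus control and about 15% for the three-arm test. Both run somewhat higher with unequal kebele sizes or a district term. This barely depends on the ICC. With kebele ignored, the error is about 16–21% for a single outcome, and that figure does depend on the derived ICC of 0.055.

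The assumptions are a two-sided 5% level, roughly normal outcomes and six kebeles per arm. The matter should be settled before analysis, but it ranks below a mandatory correction, because its size depends on the variance and reference distribution actually used.

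**What to change.** In section 3.14, name kebele as the clustering unit and base conclusions on one method valid for 18 clusters, chosen before outcome data are seen:

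- **Kebele means.** For birth weight, compare the 18 kebele means by arm: F on 2 and 15 df for three arms, or t on 16 df if the intervention arms are pooled, with one df fewer if district is included. For hemoglobin, use kebele mean change or baseline-adjusted kebele means. This is the option shown above to hold 5% most closely.
- **Or corrected GEE.** Keep the GEE clustered on kebele, with a bias-corrected sandwich variance and a t or F reference on cluster degrees of freedom. Changing the reference alone does not suffice. The correction and df should be stated together, since some pairings are conservative. Confirm that the software provides them.

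State that uncorrected GEE p-values will not support conclusions. Section 3.3 describes two arms and sections 3.4 and 3.5 describe three, so the primary contrast must be settled first.

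**Cost.** Analysis wording only, with no extra women, kebeles or measurements. Intervals widen and power falls: about 72% for the three-arm test and 84% for the pooled contrast, under the reading of 0.25 in Step 5. The 80% in section 3.4 should be restated for the test chosen.

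### The GEE effect on birth weight, the primary outcome, is stated as a difference in difference, which does not exist for an outcome with no baseline value

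*Protocol*

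**What the plan says.** Section 3.14 gives one estimand to two outcomes. The linear GEE is to test "the effects of the interventions on feto-maternal outcomes (birth weight and hemoglobin level) of difference in difference". The same section also plans a between-arm analysis: "Comparison of the KAP scores, birth weight, hemoglobin level, and GWG, differences among the study arms will be done using ANOVA".

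Section 3.4 names the primary outcome and the expected effect: "we expect a mean birth weight change of 100 gm (the primary outcome) in the intervention groups (from 2975 g to 3075 g".

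The timing of measurement is in three other places:

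- Enrolment (section 3.5): "A total of 348 first-trimester pregnant women will be enrolled at baseline".
- Baseline content (section 3.8): "data on socio-demographic characteristics, obstetrics history, MUAC, Hgb level, and 24-hour recall minimum women dietary diversity scores".
- End line (section 3.8): "The end-line data will be collected after the mother gave birth, just within 24 hrs".

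For hemoglobin, section 3.13 states: "Hemoglobin will be measured at baseline and end line".

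**The concern.** A difference in difference is the change over time in one arm minus the change over time in another. It needs a value of the same outcome before the intervention and another after it. Hemoglobin has both. Birth weight has one value per pregnancy, seen only at the end, so there is no earlier value to subtract.

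This is not a detail that a protocol may leave to a statistical analysis plan. The protocol states an estimand for its primary outcome, and its own data schedule cannot supply it. The analyst will have to replace the stated quantity with another. If the replacement is not written down before the data are seen, the primary effect is open to question over what was prespecified. The wording of section 3.4, which describes birth weight as changing from one value to another, adds to the ambiguity.

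**Working it through.** The point is structural. The protocol gives no figure for this estimand that could be reproduced, and the planned total of 348 women does not enter the argument.

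**1. Which outcomes have a before and an after value?**

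| Outcome in the GEE sentence | Baseline (first trimester) | End line (within 24 hours of birth) |
|---|---|---|
| Birth weight | none listed in section 3.8; cannot yet exist | one value |
| Hemoglobin | yes (sections 3.8, 3.13) | yes (section 3.13) |

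**2. What the model can identify for birth weight.** Write the difference-in-difference model for two arms as

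E(Y) = b0 + b1·A + b2·T + b3·A·T,

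where A is arm, T is time (0 baseline, 1 end line) and b3 is the effect.

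- Birth weight is recorded only at T = 1. The T column then equals the intercept column, and the A·T column equals the A column. The design matrix has rank 2 of 4, so b2 and b3 are not estimable.
- With three arms there are six columns: intercept, two arm indicators, time and two interactions. The rank is 3 of 6.
- Hemoglobin is recorded at T = 0 and T = 1. The two-arm matrix has rank 4 of 4, so b3 is estimable.

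**3. What is left for birth weight.** The rank of 3 in the three-arm case corresponds to the control mean and two arm contrasts. Once the redundant time terms are removed, the GEE estimates the difference in mean birth weight between arms at delivery. The planning effect in section 3.4, 3075 − 2975 = 100 g, can be read as such a between-arm difference, because no woman in the trial has two values between which a change could be taken.

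**4. Could another baseline rescue the wording?**

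- Birth weights per kebele from before the intervention would allow a cluster-level difference in difference. The protocol plans no such data.
- A previous child's birth weight is not named in the baseline data of section 3.8 or among the obstetric factors in section 3.6.2. The latter list is open-ended, but such a value would belong to another child and would be absent in first pregnancies.

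**5. Hemoglobin: efficiency only.** Let r be the correlation between baseline and end line, and assume equal variance s² at the two times. Per woman:

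- variance of the change score: 2s²(1 − r)
- residual variance after regression on baseline: s²(1 − r²)
- ratio: (1 − r²) / [2(1 − r)] = (1 + r)/2

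| r (assumed) | Ratio | Reduction |
|---|---|---|
| 0.3 | 0.65 | 35% |
| 0.5 | 0.75 | 25% |
| 0.7 | 0.85 | 15% |

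The protocol gives no value for r. These are individual-level figures. The gain in the trial's standard error also depends on the variance between the 18 kebeles.

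**The case against.** The strongest reply is that this is loose wording. The phrase comes at the end of a sentence that lists two outcomes, it fits hemoglobin, and it may have been carried over to birth weight without thought. A linear GEE on birth weight still yields a between-arm effect once the phrase is removed. That is fair as to intent and as to the size of the repair. It does not remove the error, because the sentence as written governs both outcomes and one of them is primary.

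Three stronger readings are tempting, and the document does not support them.

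- *The primary outcome has no workable analysis.* A reader might infer this from the failed rank. But only the time and interaction terms fail. The arm contrasts remain estimable, and section 3.14 lists an ANOVA of birth weight as well.
- *The trial must fall back on an ANOVA that ignores clustering, or on a model chosen after the data are seen.* Nothing in section 3.14 makes the ANOVA a substitute for the GEE; the two are planned side by side. Whether that ANOVA allows for kebele is a separate question.
- *Difference in difference is also wrong for hemoglobin.* It is not. Hemoglobin is measured twice and the effect is estimable. In a randomised trial the estimator is valid, and the case for baseline adjustment is one of precision.

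It would also go too far to prescribe similar linear models for MUAC and dietary diversity here. The GEE sentence does not cover them. Section 3.11 defines a threshold of at least 5 of 10 food groups and section 3.12 uses MUAC to assess wasting, so a linear model may not be what is intended for either.

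**Conclusion.** The point holds for the GEE estimand of birth weight. A difference in difference cannot be computed for an outcome that is seen once, after delivery, and the protocol plans no substitute baseline. This conclusion follows from the measurement schedule alone and needs no numerical assumption. Its reach is limited: the stated estimand is wrong, while an end-line comparison between arms remains possible.

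For hemoglobin there is no error, only a gain in precision available from data already planned. Its size, an individual-level variance ratio of 0.65 to 0.85, rests on an assumed r of 0.3 to 0.7 and on equal variances at the two times. It should not be read as the gain in the trial's actual standard error.

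**What to change.** In section 3.14, separate the two outcomes.

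- **Birth weight:** remove difference in difference. Define the effect as the difference between arms in mean birth weight at end line, from a linear GEE clustered on kebele, with arm and agro-ecological block (the randomisation block of section 3.5) as terms.
- **Hemoglobin:** difference in difference may stay. The better choice is to regress end-line hemoglobin on arm, the woman's own baseline hemoglobin and block, in the same clustered model.

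It would help to reword the expected effect in section 3.4 as a difference between arms, so that the two sections agree.

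The cost is one sentence for birth weight and one for hemoglobin. No new data are needed, and nothing changes in conduct or sample size.
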